### Study setting

This trial is to be conducted in approximately 16 trauma receiving hospitals across Australia in at least 4 states: Queensland, New South Wales, Victoria and Western Australia. Participating hospitals do not have a dedicated trauma service or formalised process for review of admitted trauma patients.

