### Randomisation

Participating hospitals (clusters) will be 1:1 randomised to either immediate (Group 1) or delayed (Group 2) introduction of TTS (Figure 1), using computer-generated random number function. Group 1 will implement formalised TTS in the first 12 months, with continuation of formalised TTS in the second 12 months. Group 2 hospitals will continue routine trauma care in the first 12 months followed by implementation of formalised TTS in the second 12 months. A statistician not involved with the data collection will be involved to conduct the randomisation. Results of the randomisation will be communicated to the operations manager of the study, who will inform the participating hospitals of the allocation. All patients of individual hospitals will receive the same treatment arm.

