### The intervention

The primary intervention will be at the hospital level and outcomes will be measured at the patient level. The intervention will consist of the following:The implementation of a formalised TTS form (Additional file 1: Appendix A)*,* used in two previous studies [15,16]). This form prompts documentation for relevant features of history (such as mechanism of injury) and physical examination of relevant body regions. Furthermore, the form prompts for review and documentation of relevant pathology and imaging results. The final part of the form includes a (new) injury list.All medical and nursing staff on trauma admitting wards will attend two education sessions on the rationale and use of the TTS form, provided by a chief or associate researcher in small-group work-shop format.Key stake holder engagement (Hospital executives, Directors of trauma admitting units; Emergency Department, General Surgery, Orthopaedic Surgery, Neurosurgery, Intensive Care Unit) with a clear directive to all levels of medical and nursing staff for compliance with training and education sessions and mandatory TTS form completion as part of routine care within 24 hours of admission.

Standard (existing) care will be at the discretion of the trauma admitting teams of the control hospitals. Standard care is defined as performing a clinical examination based on clinical judgment and without standardised forms. Data collection forms and procedures will be identical for both study arms. A TTS in the intervention phases is defined as completion of the formal TTS form within 24 hours of admission, where during standard care it is defined as a documented tertiary survey as part of a clinical examination within 24 hours of admission. A review of the previously known injuries only is NOT a tertiary survey.

Based on our own descriptive data [15,16], routine TTS are performed in approximately 25% of admitted multi-trauma patients. To truly assess the effect of a formalised TTS on missed injuries, the compliance in the intervention hospitals is aimed to be >90%, but will need to be at least 75% to be deemed an effective implementation of the intervention.

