### Outcome measures

The primary outcome is Type III missed (Post-hospital discharge) injury rate. This study aims to compare the effect of a formalised TTS compared to routine care on missed injury rates after hospital discharge (type III).

Secondary outcomes are:Maintenance of intervention effect (comparing two 12-month periods in Group 1)*During Hospital Stay*In-hospital missed injury rate (Type I and II combined)Proportion of TTS performedHospital bed days, ICU bed days*During Follow-up (1,6 and 12 months post hospital discharge)*Clinically significant missed injuries (as determined by expert panel)Interventions required for delayed diagnosis (Type I and II) or missed injuries (Type III)Diagnostic imaging usage (CT, MRI, USS)Predefined complications of care and injury (see above)Readmissions to hospitalDays off workQuality of life (EQ-5D-5 L)Days off workMortality

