### Statistical analysis and sample size

The primary analysis will be by intention-to-treat (ITT). Per-protocol analyses will also be performed, based on all patients completing 1, 6 and 12 months follow-up. Based on our prospective study [16], comparing routine care with the formalised TTS group, we anticipate a decrease in post discharge (Type III) injuries from 14% to 9%. We foresee this will be accompanied by an increase of in-hospital injury detection (missed injury Type I and II combined) from 4% to 9%.

The sample size for a cluster-randomized trial requires adjustment of the number of patients that a corresponding individually randomized trial would have needed. This is due to variation between the clusters, and results in a correction using the intra-cluster correlation coefficient (ICC) [21]. Using an alpha of 0.05 and a power of 0.80, a sample size of 638 patients per group, with 1-year follow-up completed, would be required if individually randomised. Our previous study [17] achieved a telephone follow-up rate of 40% at 6 months. Extrapolating a similar conservative follow-up rate at 12 months, a total of 3,190 patients will be required (1,595 for each cohort) to answer the primary hypothesis. To separately answer a before-and-after comparison in Group 2 hospitals a similar sample is required. This results in a sample of 6,380 patients, with complete 1-year follow-up in at least 2,552. Since approximately 0.4% [22] of all ED presentations consist of multi-trauma patients, approximately 1,600,000 ED presentations will be required. For an approximate 24-month recruitment period, this equates to 16 hospitals that have an average annual census of 50,000 presentations. Based on this sample size, the maximum ICC that can be present before the power of the study is reduced below 80% is dependent on cluster size and numbers and presented in Table 3*.*

**Table 3 Tab3:** **Approximate maximum intra-class correlation (ICC) for various cluster sizes and number of intervention hospitals to answer primary hypothesis**

**Number of intervention (and control) hospitals**	**Average size of cluster**	**Maximum ICC to have 80% power to detect 5% difference**
8	400	0.01
15	400	0.02
21	400	0.03
9	300	0.01
15	300	0.02
22	300	0.03
10	200	0.01
16	200	0.02
23	200	0.03

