This calculation is consistent with a previous study specifically examining the ICC in trauma receiving hospitals. ICC varied depending on outcome, but the average ICC for blunt trauma the ICC was 0.01 [23]. Assuming an average cluster size of 250 patients, this would mean a total of 3,440 patients would require recruitment (approximately 14 clusters) for the primary hypothesis.

The study is adequately powered for the primary hypothesis, and for several secondary outcomes, such as pre- and post-comparison in Group 2, but not for the pre- and post- comparison in Group 1, measuring maintenance of the intervention effect.

De-identified data will be analysed using SPSS v20.0 software (SPPS Inc, Chicago, IL, USA). For continuous variables, we will use an independent *t*-test and chi-square test will be used to compare differences in proportions. All results will be presented with 95% confidence intervals.

Health economic analyses will include a within trial incremental cost-effectiveness evaluation of formal TTS versus standard care. The outcome measure, incremental cost-effectiveness ratio, directly compares the difference in costs between the formal TTS and standard care with the difference in health related quality of life. Health-related quality of life will be measured in quality adjusted life years (QALYs) derived from changes in EQ-5D-5 L measured at multiple time points. A cost-effective threshold of $AUD 50,000 per QALY will be used to determine whether the intervention was cost-effective and a cost-effectiveness acceptability analysis will be conducted using a range of threshold values from $20,000 to $100,000. A 95% confidence interval around the incremental cost-effectiveness ratio will be estimated using bias-adjusted bootstrapping. In addition, sensitivity analyses and sub-group analyses will be conducted to identify the parameters and patient characteristics that affect the likelihood of the intervention being cost-effective. A *P* value of 0.05 or less will be deemed statistically significant.

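### Hospitals are randomised, but the tests named make no allowance for clustering; for the primary comparison the chi-square test's type I error is about 14% if the cited ICC of 0.01 applies

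*Protocol article*

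**What the plan says.** The protocol article's Randomisation section makes the hospital the unit of allocation: "Participating hospitals (clusters) will be 1:1 randomised to either immediate (Group 1) or delayed (Group 2) introduction of TTS". It adds: "All patients of individual hospitals will receive the same treatment arm". Study setting gives about 16 hospitals, so about 8 per arm. The intervention section separates the two levels: "The primary intervention will be at the hospital level and outcomes will be measured at the patient level". The primary outcome is a proportion: "The primary outcome is Type III missed (Post-hospital discharge) injury rate".

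Statistical analysis and sample size explains that a cluster trial needs more patients than an individually randomised one: "This is due to variation between the clusters, and results in a correction using the intra-cluster correlation coefficient (ICC"). Table 3 then considers ICCs of 0.01 to 0.03, and the text below it cites an average of 0.01 for blunt trauma.

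The same section then names its hypothesis tests. Continuous variables get an independent t-test, and a "chi-square test will be used to compare differences in proportions". Results carry 95% confidence intervals, and P of 0.05 or less counts as significant. No mixed model, generalised estimating equation, hospital-level summary or design-effect adjustment is stated.

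**The concern.** A chi-square test on patient counts takes its standard error from the number of patients. When whole hospitals are allocated, the comparison also carries the chance difference between one set of 8 hospitals and another. With 16 hospitals, only 14 degrees of freedom are available to estimate that variation. A test that leaves it out gives P values that are too small and intervals that are too short.

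The plan allows for clustering when setting the sample size and not when testing. The Discussion says the survey should be adopted widely if effective and abandoned if not, so a chance difference between hospitals could be read as an effect of the survey and change practice.

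**Working it through.** **Inputs from the protocol article**
- Anticipated Type III rates of 14% and 9%, alpha 0.05, power 0.80, 638 completers per group, 40% follow-up, 1,595 recruited per group (Statistical analysis and sample size).
- About 16 hospitals, 1:1, so 8 per arm (Study setting; Randomisation).
- ICC 0.01, the cited blunt-trauma average; Table 3 spans 0.01 to 0.03.

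**1. The plan's own figure.** With pooled variance, two-sided:

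n = [1.96 × √(2 × 0.115 × 0.885) + 0.842 × √(0.14 × 0.86 + 0.09 × 0.91)]² / 0.05² = 638 per group.

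Then 638/0.40 = 1,595, as stated. So 638 is the number for individual randomisation, without a design effect.

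**2. Analysed cluster size.** Primary outcome: m = 638/8 ≈ 80 completers per hospital. In-hospital outcomes: m = 1,595/8 ≈ 199.

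**3. True size of the unadjusted test.** Design effect DE = 1 + (m − 1) × ICC. Type I error = 2 × [1 − Φ(1.96/√DE)].

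At m = 80 and ICC 0.01: DE = 1 + 79 × 0.01 = 1.79, and 2 × [1 − Φ(1.96/1.338)] = 14.3%. The reported interval is 1/√1.79 = 0.75 of its proper width, so about 25% too narrow.

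| Analysed per hospital | ICC | DE | Type I error |
|---|---|---|---|
| 80 | 0.001 | 1.08 | 5.9% |
| 80 | 0.005 | 1.39 | 9.7% |
| 80 | 0.01 | 1.79 | 14.3% |
| 80 | 0.02 | 2.58 | 22.2% |
| 80 | 0.03 | 3.36 | 28.5% |
| 100 (40% of the 250 per cluster also used in the text) | 0.01 | 1.99 | 16.5% |
| 199 (in-hospital outcomes) | 0.01 | 2.98 | 25.7% |

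**4. Simulation check.** Beta-binomial hospital rates, 8 versus 8 hospitals, no true effect, 100,000 runs, ICC 0.01. At m = 80 the chi-square test rejected in 14.1% (rate 14%) and 14.5% (rate 9%) of runs. At m = 199 it rejected in about 25%. A t-test on the hospital proportions rejected in 4.9% to 5.0% of the same runs.

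**5. Before-and-after comparisons.** Here the same hospitals supply both periods. Let c be the correlation of a hospital's effect between periods; the document does not give it. Then DE = 1 + (m − 1) × ICC − m × ICC × c. At m = 80 and ICC 0.01:
- c = 1: DE = 1.79 − 0.80 = 0.99, type I error 4.9%.
- c = 0.9: DE = 1.79 − 0.72 = 1.07, 5.8%.
- c = 0.8: DE = 1.79 − 0.64 = 1.15, 6.7% (simulated).
- c = 0.5: DE = 1.79 − 0.40 = 1.39, about 9.6% (simulated).
- c = 0: DE = 1.79, about 14%.

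**The case against.** - **An article condenses a fuller plan.** That would excuse silence on the model. Here the article names particular tests, in a sentence without qualification that covers the primary outcome. The objection fails.
- **The t-test's unit is not stated.** An independent t-test on hospital means would be a valid cluster analysis. This stands as a caution: the patient-level reading follows from the intervention section, not from the test sentence itself. The chi-square test leaves less room, and it is the one that applies to the primary outcome.
- **The ICC of 0.01 is not for this outcome.** The text itself says that the ICC varied by outcome. This stands. The 14% is conditional, and at ICC 0.001 the inflation is slight (5.9%). Equal cluster sizes and 40% follow-up at 12 months are further assumptions.
- **All secondary results are too optimistic.** A reader might infer this, including for maintenance of effect in Group 1 and the before-and-after comparison in Group 2. The document does not support it. In those contrasts a stable hospital effect cancels, and the unadjusted test is then about nominal (4.9%). Inflation appears only as hospital effects change between periods, and the document gives no figure for that.

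**Conclusion.** The plan is wrong as written. It names a test for the primary outcome that does not fit hospital randomisation, and it contradicts the plan's own statement that clustering needs correction.

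For the parallel comparison of Type III injury, the type I error is about 14% instead of 5%, and intervals are about 25% too narrow. This assumes 8 equal hospitals per arm, about 80 completers in each, and ICC 0.01. Over ICCs of 0.001 to 0.03 the error runs from about 6% to 29%. For in-hospital outcomes with about 200 patients per hospital it is about 25%, if the same ICC applies to them.

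The before-and-after analyses are mis-specified because they ignore that the same hospitals contribute to both periods. Their error runs from about nominal to inflated and cannot be fixed from the document.

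**What to change.** Replace the sentence on tests in Statistical analysis and sample size with the following:

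- **Primary outcome:** one named analysis that suits about 8 clusters per arm. An example is a t-test on the 16 hospital proportions (14 degrees of freedom), giving a risk difference with 95% confidence interval.
- **Sensitivity analysis:** a mixed-effects logistic model with a hospital random intercept and small-sample degrees of freedom. It estimates a conditional odds ratio, a different quantity, so it should not be described as equivalent to the primary analysis.
- **Continuous outcomes:** a linear mixed model with a hospital random effect, or a comparison of hospital means.
- **Before-and-after contrasts:** a paired hospital-level analysis, or a mixed model with random hospital and random hospital-by-period effects.
- **Intervals:** derive every 95% confidence interval from these analyses.

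The cost is a change of wording and slightly more analysis work. Intervals for the between-group comparison become wider: at ICC 0.01 and 80 completers per hospital by a factor of about √1.79 = 1.34, and a little more for the 14 degrees of freedom. That is the precision the design actually has. No new data are needed, and Trial status says recruitment has not begun, so the change can precede any data.

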A retrospective study [15] in our Australian level II trauma facility found poor compliance to routine TTS and identified a lack of data regarding post-discharge missed injuries. A subsequent, pragmatic, prospective before-and-after study [16] evaluated the implementation of a formalised TTS procedure by measuring missed injury rates during a hospital stay (Type I and II) as well as after discharge (Type III). The in-hospital missed injury rate (Type I and II combined) was similar for both groups (Pre: 3.8% versus Post: 4.8%), as were Type III missed injuries at 1 month (Pre: 13.7% versus Post: 11.5%), and 6 months (Pre: 3.8% versus Post: 3.3%). Although there was a substantial increase in tertiary survey performance (27% versus 42%, *P* < 0.001), this may not have been enough to detect any potential differences in missed injury rates if they exist.

Missed injuries may be minor or only require conservative treatment. Therefore, the focus ideally should be on clinically significant missed injuries. Few studies have defined ‘clinically significant’ *post hoc*, [7,11,12] with most studies not providing any definition. Whilst the incidence of clinically significant missed injuries is unknown, they are more likely to lead to prolonged morbidity or mortality. Although mortality as a result of missed injuries is conceivably rare, our prospective study indicated that approximately 1% of the cohort required a surgical intervention for injuries detected after the hospital discharge. [16].

Current international guidelines such as Early Management for Severe Trauma (EMST) do mention consideration of tertiary surveys, but do not mandate or formalise their implementation. [17] This may be the result of their focus on *early* trauma care, where the tertiary survey by can be conducted up to 24 hours after ED assessment.

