### Aims and hypotheses

Our primary aim is to determine whether the implementation of a formalised TTS will decrease missed injuries post hospital discharge (Type III injuries) and, as secondary aim, increase injury detection in hospital (Type I and II injuries combined). We further hypothesise that the intervention effect will be maintained and that the intervention would lead to decreased clinically significant missed injuries as judged by a blinded expert panel, decreased hospital and ICU bed days, decreased readmissions to hospital, improved quality of life and decreased time off work. We expect complications of the injuries to be the same, but complications of care to be less. If no difference between injury rates is found, we hypothesise that both arms will be equivalent in resource utilisation (ICU and hospital bed days, investigations ordered, interventions required).

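### The planned bootstrap confidence interval for the ICER is unreliable if the QALY difference is small relative to its error, which is plausible here; net monetary benefit with an interval that respects hospital randomisation should replace it

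*Protocol article*

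**What the plan says.** The health economic paragraph of the section Statistical analysis and sample size (protocol article) names the ICER as the outcome measure of a within-trial evaluation. Its effect side is "quality adjusted life years (QALYs) derived from changes in EQ-5D-5 L measured at multiple time points". Three things are then fixed:

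- the interval: "A 95% confidence interval around the incremental cost-effectiveness ratio will be estimated using bias-adjusted bootstrapping";
- the decision rule: "A cost-effective threshold of $AUD 50,000 per QALY will be used to determine whether the intervention was cost-effective";
- the uncertainty analysis: "a cost-effectiveness acceptability analysis will be conducted using a range of threshold values from $20,000 to $100,000".

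The article gives no expected QALY difference, no SD for QALYs or costs, and no ICC for either. It does not state the resampling unit of the bootstrap. Under Aims and hypotheses it hypothesises "decreased readmissions to hospital, improved quality of life and decreased time off work", without sizes. Under Background it notes: "Missed injuries may be minor or only require conservative treatment".

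**The concern.** A bootstrap interval for a ratio is read off by ordering the replicate ratios. That works only if the denominator keeps its sign. Once replicates fall on both sides of zero QALYs, the same number carries opposite meanings. A saving of AUD 200 with a gain of 0.005 QALY gives -200/0.005 = -40,000 (dominant). An extra AUD 200 with a loss of 0.005 QALY gives 200/(-0.005) = -40,000 (dominated). Replicates with a denominator close to zero run towards plus or minus infinity. Bias adjustment moves the percentiles that are read off; it does not restore an order that is missing.

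The Discussion ties wide implementation or abandonment of the TTS to whether it is effective or cost-effective. A funder could therefore be handed an interval that does not bound the quantity it claims to bound. This is a method the article states, not a detail left to a fuller plan.

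**Working it through.** **1. The plan's own sample size.** For 14% versus 9%, two-sided alpha 0.05, power 0.80, pooled variance and mean proportion 0.115:

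n = [1.96·√(2·0.115·0.885) + 0.842·√(0.14·0.86 + 0.09·0.91)]² / 0.05² = (0.884 + 0.379)² / 0.0025 ≈ 638 completers per group.

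With 40% follow-up, 638/0.4 = 1,595 per group, 3,190 for the primary comparison and 6,380 in all. The stated figures reproduce.

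**2. Inputs for the economic check.**
- From the article: 638 completers per arm; 16 hospitals, so 8 per arm and about 80 completers each; ICC 0.01 (an average for blunt trauma outcomes, borrowed here); a 5-point fall in Type III injuries.
- Assumed: QALY SD 0.25 (range 0.15 to 0.30); ICC 0 to 0.02; a loss of 0.05 to 0.2 QALY over the year per missed injury. The mean gain is then 0.05 × 0.05 = 0.0025 to 0.05 × 0.2 = 0.01 QALY.

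**3. Standard error and share below zero.** SE = SD·√[(2/n)·(1 + (m − 1)·ICC)].
- SD 0.25, ICC 0: 0.25·√(2/638) = 0.0140.
- SD 0.25, ICC 0.01: design effect 1 + 79·0.01 = 1.79; SE = 0.25·√(2/638·1.79) = 0.0187. At a gain of 0.005, Φ(−0.005/0.0187) ≈ 0.39.
- Most favourable corner (SD 0.15, ICC 0, gain 0.01): SE 0.0084, share Φ(−1.19) ≈ 0.12.
- Least favourable corner (SD 0.30, ICC 0.02, gain 0.0025): SE 0.027, share Φ(−0.09) ≈ 0.46.

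The range is therefore about 12% to 46%.

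**4. What would keep the denominator clear of zero.** The gain would have to reach 1.96·SE. At SD 0.25 and ICC 0.01 that is 0.037 QALY, or 0.037/0.05 ≈ 0.73 QALY saved within a year per missed injury averted. At ICC 0 it is 0.55; at SD 0.15 and ICC 0 it is still 0.33.

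**5. Behaviour of the interval.** The simulation used 8 hospitals per arm with 80 completers each, 1,500 runs per scenario and 1,000 draws per run. QALY SD was 0.25, cost SD AUD 8,000 and the true cost difference AUD 200. Costs and QALYs were independent. Patients were resampled by a normal approximation, and the interval was bias-corrected without acceleration.

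| True gain (QALY) | Coverage, ICC 0 | Coverage, ICC 0.01 | Median width, ICC 0 (AUD/QALY) | Median width, ICC 0.01 (AUD/QALY) |
|---|---|---|---|---|
| 0.0025 | 59% | 54% | 2.49 million | 1.48 million |
| 0.005 | 68% | 65% | 3.03 million | 1.90 million |
| 0.01 | 76% | 74% | 1.57 million | 1.10 million |
| 0.025 | 93% | 81% | 227,000 | 304,000 |
| 0.05 | 95% | 85% | 45,000 | 47,000 |

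At ICC 0 patient resampling is correct, so the shortfall in that column comes from the ratio alone.

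**6. Net monetary benefit in the same simulation**, at AUD 50,000 per QALY. Patient resampling covered about 95% at ICC 0 but about 85% at ICC 0.01. A plain hospital-level percentile bootstrap covered about 90% to 91% at both.

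**7. What a reader would get instead.** At a gain of 0.005, net benefit is 50,000·0.005 − 200 = AUD 50 per patient. At ICC 0.01 for both components, SE = √[(50,000·0.0187)² + (8,000·√(2/638·1.79))²] ≈ √(936² + 599²) ≈ 1,112. With a t quantile on 14 degrees of freedom (2.145), the interval is about AUD −2,330 to 2,430: wide, but finite and readable.

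**The case against.** The strongest reply is that the decision does not need the ICER interval. The acceptability value at a given threshold is the probability that net monetary benefit at that threshold is positive, and it is well defined in all four quadrants. A reader might infer that the whole economic conclusion rests on the ICER interval. The article does not support that, because the AUD 50,000 threshold and the curve from AUD 20,000 to 100,000 stand beside it. What stands of the concern is that the curve does not validate the stated interval, and that no net-benefit estimate with an interval is named.

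A reader might also infer that the trial expects almost no QALY difference. It does not say so. It hypothesises improved quality of life, and the clause "If no difference between injury rates is found" is a conditional about resource use. The near-zero difference is an inference from assumed utility losses. It also credits all the gain to the fall in Type III injuries, although fewer complications of care and readmissions are hypothesised too. A gain near 0.05 QALY would remove the ratio problem. Through missed injuries alone, however, it would need 0.05/0.05 = 1 whole QALY per injury averted.

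Finally, a reader might infer that patients will be resampled as if independent. The resampling unit is not stated, and a condensed article may leave it to a fuller plan. It is a risk to close off, not an error shown. The fact that cost-effectiveness is absent from the listed outcome measures limits the weight of the point but does not remove it.

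**Conclusion.** The point holds conditionally. The article fixes an interval method that fails when the QALY difference may change sign, and its own effect size and completer numbers make that plausible. The share of the sampling distribution below zero (about 12% to 46%), the coverage (about 54% to 76% against a nominal 95%) and the median widths of AUD 1.1 to 3.0 million per QALY all rest on gains of 0.0025 to 0.01. The coverage and widths further rest on SD 0.25, ICC 0 or 0.01 and the assumed costs. None of the QALY or cost inputs is in the article, and the ICC is borrowed from other outcomes. If the true gain were about 0.05 QALY with no clustering, the planned interval would be sound. The acceptability analysis softens the consequence for the decision. The point does not touch the primary analysis or the design, but it is worth correcting because the change is cheap.

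**What to change.** Replace the confidence interval for the ICER with incremental net monetary benefit at AUD 50,000 per QALY and its 95% interval. Obtain that interval by a method that respects randomisation by hospital: for example, a bivariate mixed model for costs and QALYs, or a bootstrap that resamples hospitals. Either needs a small-sample correction, since a plain hospital-level percentile bootstrap reached only about 90% to 91% coverage with 8 hospitals per arm. Derive the acceptability curve over AUD 20,000 to 100,000 from the same method. Report the ICER as a point estimate alongside the cost-effectiveness plane.

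The cost is a change of wording and slightly more analysis work, with possibly wider intervals. Data collection is unchanged, and the Trial status section says recruitment has not begun.
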